### Safety monitoring

3.8

AEs will be assessed at each treatment session and at each study contact during the intervention period. Their severity, duration, relationship to the intervention, actions taken, and outcomes will be documented in the case report form (CRF). Potential intervention-related adverse events may include transient soreness, skin irritation, or bruising at treatment sites. If a participant experiences an adverse reaction, appropriate medical care will be provided promptly, and the event will be recorded in detail in the CRF. Decisions regarding treatment interruption or withdrawal from the study will be made by the principal investigator in accordance with the study protocol and institutional requirements. Serious adverse events (SAEs) will be documented immediately, assessed for severity and relatedness by the principal investigator, and reported to the ethics committee in accordance with institutional requirements.

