**Figure 1 fig1:**
[figure not shown]
The flow chart of this trial.

**Table 1 tab1:** Study schedule.

Time points	Study period					
	Enrollment	Treatment			Follow-up	
	Week −1	Week 0	Week 4	Week 8	12 weeks post-treatment	24 weeks post-treatment
Enrollment						
Eligibility screen	✓					
Informed consent	✓					
Demographic characteristics	✓					
Medical history	✓					
Allocation		✓				
Physical Examination	✓					
Comorbidities	✓					
Interventions						
Tuina		✓	✓	✓		
Standardized usual care		✓	✓	✓		
Outcomes						
FS-14		✓	✓	✓	✓	✓
SF-36		✓	✓	✓	✓	✓
Pain-VAS		✓	✓	✓	✓	✓
PSQI		✓	✓	✓	✓	✓
SAS		✓	✓	✓	✓	✓
SDS		✓	✓	✓	✓	✓
GSRS		✓	✓	✓	✓	✓
BSFS		✓	✓	✓	✓	✓
HGS		✓	✓	✓	✓	✓
fMRI		✓		✓		
MRS		✓		✓		
Blood and fecal metabolites		✓		✓		
Metagenomic Sequencing		✓		✓		
Assessments						
Patient compliance		✓	✓	✓		
Adverse events		✓	✓	✓		
Concomitant medications		✓	✓	✓	✓	✓

FS-14, Fatigue Scale-14; SF-36, 36-Item Short Form Health Survey; Pain-VAS, Visual Analog Scale of Pain; PSQI, Pittsburgh Sleep Quality Index; SAS, Self-Rating Anxiety Scale; SDS, Self-Rating Depression Scale; GSRS, Gastrointestinal Symptom Rating Scale; BSFS, Bristol Stool Form Scale; HGS, Handgrip strength; fMRI, functional Magnetic Resonance Imaging; MRS, Magnetic Resonance Spectroscopy; Weeks 0, 4, and 8 are counted from baseline; week 8 corresponds to the end-of-treatment assessment. Follow-up assessments are scheduled at 12 and 24 weeks after completion of treatment.

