#### Experimental group

3.6.1

Participants in the experimental group will receive the Tuina intervention in addition to the general trial advice provided to all participants, including maintaining their usual activity level and refraining from initiating any new CFS-related therapies during the 8-week treatment period. The Tuina intervention will be delivered twice weekly for 8 weeks (16 sessions in total), with a minimum interval of 48 h between sessions. Each session will last approximately 20 min. Any concomitant treatments and changes in medical care during the study period will be recorded in the case report forms (CRFs).

The Tuina therapy will focus on the abdomen (Conception vessel and key abdominal acupoints), back (the first line of the Bladder meridian and Back-Shu points), and lumbar region, with the aim of influencing autonomic regulation and gastrointestinal function. The intervention will be delivered by six licensed Tuina therapists, each with at least 5 years of clinical experience. Before participant enrollment, all therapists will receive unified training in the study-specific standard operating procedures.

A typical 20-min treatment session will follow a standardized sequence. In the supine position, one-finger pushing will be applied to Zhongwan (CV12), Qihai (CV6), and Tianshu (ST25) for 1 min at each point, followed by palm rubbing over the abdomen for 5 min until local warmth is achieved. Kneading will then be performed at CV12, CV6, and ST25 for 1 min at each point, followed by pressing-kneading at Zusanli (ST36) and Sanyinjiao (SP6) for 1 min at each point. In the prone position, one-finger pushing and rolling will be applied along the first line of the Bladder meridian on the back, with emphasis on the Back-Shu points of the five zang organs, including Feishu (BL13), Xinshu (BL15), Ganshu (BL18), Pishu (BL20), and Shenshu (BL23). Linear rubbing will then be performed along the Governor vessel and Bladder meridian until local warmth is achieved. Acupoints will be located in accordance with GB/T 12346–2021 (Naming and Positioning of Acupoints). Representative images of the standardized Tuina procedures are provided in Supplementary Figure 1. Detailed acupoint information and intervention procedures are provided in Supplementary Table 1.

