#### Control group

3.6.2

The control group will receive standardized usual care. Participants in the control group will receive health education and symptom-oriented management once weekly for 8 weeks, with each session lasting approximately 40 min. The program will cover balanced diet, sleep hygiene, stress management, psychological support, and tailored symptom management advice when clinically indicated. To reduce contamination, additional interventions specifically targeting fatigue, such as newly initiated pharmacotherapy, acupuncture, or herbal prescriptions, will not be permitted during the 8-week treatment period unless deemed clinically necessary. Stable pre-existing medications may be continued. Standardized usual care will be delivered by two TCM attending physicians who are licensed clinicians and have completed study-specific training and Good Clinical Practice certification. Concomitant medications and any rescue treatments will be recorded at each visit. Staff qualifications, training records, and adherence to the intervention protocol will be documented and audited.

Participant blinding is not feasible because of the nature of the Tuina intervention. The control group will receive health education and symptom-oriented management with standardized contact procedures and approximately matched total contact time, which is intended to help reduce imbalances in attention and trial engagement between groups. However, because treatment frequency and tactile contact cannot be matched, residual differences in treatment expectancy and performance effects may remain. This comparator was chosen to reflect current clinical management for CFS, in which symptom-oriented and supportive care remains the predominant non-pharmacological management approach. The study therefore evaluates standardized Tuina in comparison with standardized usual care, rather than against an inert, no-treatment, or fully attention-matched sham condition.

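### Adverse-event enquiry follows the session schedule (16 Tuina v 8 usual-care sessions) and stops with treatment, so by-arm summaries of brief non-serious events are open to detection bias against Tuina, and late non-serious events are not systematically sought

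*Protocol article*

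**What the plan says.** Section 3.8 (Safety monitoring) fixes when AEs are sought: "AEs will be assessed at each treatment session and at each study contact during the intervention period". Serious AEs have a separate rule in the same section. They are documented as soon as they arise, with no link to sessions and no stated end date.

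The session schedules differ by arm. Section 3.6.1: "The Tuina intervention will be delivered twice weekly for 8 weeks (16 sessions in total"). Section 3.6.2: "Participants in the control group will receive health education and symptom-oriented management once weekly for 8 weeks".

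In Table 1 the row "Adverse events" is ticked at weeks 0, 4 and 8 and left blank at 12 and 24 weeks post-treatment. The concomitant-medication row is ticked at both of those visits, as are all nine clinical outcome measures.

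Section 3.6.2 acknowledges the difference in frequency, but only for its effect on expectancy and performance: "because treatment frequency and tactile contact cannot be matched, residual differences in treatment expectancy and performance effects may remain". It does not mention AE ascertainment.

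**The concern.** When enquiry is tied to sessions, the arm with more sessions is asked more often. The events that section 3.8 itself expects from Tuina are soreness, irritated skin or bruises where treatment was applied. Soreness and skin irritation in particular may have gone by the next weekly contact, and such events are the most sensitive to how often people are asked. Even with identical true harm, an AE table by arm could show more events with Tuina simply because of the schedule.

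The second part is timing. The Discussion presents the 24-week follow-up as a way to judge whether benefit lasts, and efficacy is measured at both follow-up visits. Non-serious AEs are not sought at those visits. The Introduction stresses post-exertional exacerbation as a hazard in this population, yet section 3.7.1 describes the post-exertional malaise questionnaire at baseline only. AE reporting is therefore one of the few routes by which worsening of that symptom would be recorded.

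At stake is how far the trial's AE data can inform the Introduction's suggestion that Tuina may be a low-risk option.

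**Working it through.** **Inputs from the article**
- Tuina: "delivered twice weekly for 8 weeks (16 sessions in total"), and "Each session will last approximately 20 min" (section 3.6.1).
- Usual care: "health education and symptom-oriented management once weekly for 8 weeks, with each session lasting approximately 40 min" (section 3.6.2).
- AE window: the intervention period, 8 weeks in both arms (sections 3.1 and 3.8).
- Follow-up visits: 12 and 24 weeks after treatment (Table 1).

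**Step 1. Session counts**
- Tuina: 2 × 8 = 16, which reproduces the printed figure.
- Usual care: 1 × 8 = 8 (derived; the article prints no total).
- Contact time: 16 × 20 = 320 min and 8 × 40 = 320 min. Total time is matched, but the number of occasions is not.

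**Step 2. Enquiry ratio**
- Sessions only: 16 / 8 = 2.0.
- If the week 4 and week 8 assessments are separate contacts: (16 + 2) / (8 + 2) = 18 / 10 = 1.8.

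**Step 3. What this could do to capture of events.** The article gives no reporting probabilities or recall periods, so the following are illustrations over assumed ranges, with equal true event rates in both arms.

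(a) Assume a weekly event is reported with probability p at each enquiry, independently, with two enquiries a week under Tuina and one under usual care. The capture ratio is [1 − (1 − p)²] / p = 2 − p.

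| Assumed p | Tuina | Usual care | Ratio |
|---|---|---|---|
| 0.1 | 0.19 | 0.10 | 1.9 |
| 0.5 | 0.75 | 0.50 | 1.5 |
| 0.9 | 0.99 | 0.90 | 1.1 |

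(b) Assume an event is reported only if an enquiry falls within r days of it, with enquiries every 3.5 days (Tuina) or 7 days (usual care). The ratio is min(1, r/3.5) / min(1, r/7).

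| Assumed r (days) | Tuina | Usual care | Ratio |
|---|---|---|---|
| 2 | 0.57 | 0.29 | 2.0 |
| 3.5 | 1.00 | 0.50 | 2.0 |
| 5 | 1.00 | 0.71 | 1.4 |
| 7 or more | 1.00 | 1.00 | 1.0 |

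(c) Assume a constant probability that any enquiry yields an AE report. The proportion of participants with at least one AE is 1 − (1 − p)^16 against 1 − (1 − p)^8.
- p = 0.01: 14.9% v 7.7%.
- p = 0.02: 27.6% v 14.9%.
- p = 0.05: 56.0% v 33.7%.

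**Step 4. Share of the study without scheduled AE enquiry**
Total duration is 8 + 24 = 32 weeks, and 24 / 32 = 75% falls after the AE window closes.

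**The case against.** The strongest reply has five parts.

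1. *The effect is confined to some events.* This stands. An event that lasts, or is recalled, until the next weekly contact is captured about equally in both arms, and serious AEs do not depend on sessions. A reader might infer that every comparison of harms in this trial is biased, but the article does not support that. It also states no formal between-arm AE comparison. Any by-arm listing of brief, non-serious events would still carry the imbalance.

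2. *Late harm is not invisible.* This stands too. A reader might infer from the blank cells in Table 1 that deterioration after week 8 goes unrecorded. In fact fatigue, quality of life, pain, sleep, mood, gut symptoms, stool form and grip strength are all measured in both arms at both follow-up visits. Medications are recorded there, the rule for serious AEs has no stated end, and section 3.12 provides a safety committee. What is absent is scheduled enquiry about late non-serious AEs.

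3. *The bias runs against Tuina.* Correct. A low AE count despite more frequent enquiry would support the low-risk description. The difficulty is an excess, which could not be separated from the effect of asking more often.

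4. *Who asks is not stated.* Correct. It is tempting to say that the unblinded therapist elicits events in the Tuina arm, but section 3.8 does not say so. If treating staff did ask, that would apply in both arms.

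5. *This is a design choice, and form-level detail may sit in supplementary material.* Text and table do agree on when collection ends, so there is no contradiction. However, the timing of enquiry is a stated rule and not an omitted detail. Followed exactly, it produces the imbalance and the gap.

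**Conclusion.** The point holds in a limited form. AE enquiry is unequal by arm, 16 v 8 on sessions or 18 v 10 with two separate assessment contacts, and it ends with the intervention period. By-arm summaries of brief, non-serious AEs are therefore open to detection bias against Tuina. Non-serious AEs over the following 24 weeks are not systematically collected, although participants attend two visits in that time.

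The size cannot be fixed from the article. Under the assumed models the spurious ratio runs from about 2 for very short-lived or rarely volunteered events to about 1 for events that persist or are remembered for a week. No single value in that range is established. The counts and the end of the AE window rest on the printed text alone. The reporting probabilities and recall windows are assumptions.

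This does not affect the primary efficacy analysis. It is worth correcting because the remedy is cheap and the safety summary would otherwise be hard to interpret.

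**What to change.** **Section 3.8.** Keep the checks at each session for participant care. Base the between-arm AE summary on one identical structured question put at the same times in both arms, for example weeks 4 and 8. Include worsening of fatigue or of post-exertional malaise in that question. Report events elicited only at sessions separately. This brings the enquiry ratio for the comparison from 2.0 to 1.0.

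**Table 1.** Add AE and serious-AE enquiry to the visits 12 and 24 weeks after treatment.

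**Protecting the masking.** The assessor who collects FS-14 is meant to remain unaware of allocation (section 3.5), and a report of soreness or bruising at a treatment site could reveal it. Use a self-completed form or existing staff other than that assessor, or ask only after the outcome questionnaires are finished.

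**Cost.** A few lines in section 3.8, two additions to Table 1, a short form, and a few minutes at visits that already take place.

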### Statistical analysis

3.9

Statistical analyses will be performed using SPSS version 26.0 (IBM Corp., Armonk, NY, USA). Baseline characteristics will be summarized as mean (SD) or median (IQR) for continuous variables and as number (%) for categorical variables, as appropriate. Longitudinal outcomes will be analyzed using linear mixed-effects models including fixed effects for group, time, and group-by-time interaction. The models will be adjusted for baseline outcome values, study center, and sex, with additional prespecified covariates included where appropriate. For the primary outcome analysis, baseline FS-14 score will be included as a covariate. Secondary clinical outcomes will be interpreted with consideration of multiplicity, and exploratory omics and imaging analyses will be interpreted as hypothesis-generating. All tests will be two-sided, and a *p* value <0.05 will be considered statistically significant. The primary efficacy analysis will follow the intention-to-treat principle. A per-protocol analysis will be conducted as a sensitivity analysis. The primary comparison will be the between-group difference in change in FS-14 total score from baseline to week 8, estimated from the mixed-effects model. Missing data will be handled under the missing-at-random assumption inherent to mixed-effects models, and additional sensitivity analyses will be conducted if warranted. Because this is a multicenter trial, study center will be included in the analysis model to account for potential between-center variability. All statistical analyses will be performed with group allocation concealed until database lock. The full trial protocol is provided in this article and its online Supplementary materials.

### Metabolomics and microbiota analyses

3.10

These analyses are exploratory and hypothesis-generating, are not formally powered for confirmatory inference, and will be interpreted primarily as effect-size estimation and biological signal characterization rather than definitive hypothesis testing. These findings will not be interpreted as confirmatory efficacy evidence. Targeted metabolomics data will be analyzed using multivariate and univariate approaches to identify differential metabolites, with particular focus on the tryptophan pathway. Multivariate analyses will include principal component analysis and supervised discrimination methods, whereas univariate comparisons will be corrected for multiple testing using the false discovery rate (FDR). Pathway enrichment analyses will then be performed, and associations between metabolite changes and clinical outcomes will be examined using Pearson or Spearman correlation analyses, as appropriate.

Microbiota data will be analyzed at the levels of alpha diversity, beta diversity, and differential taxonomic abundance. Alpha diversity indices will be compared using appropriate parametric or nonparametric methods according to data distribution and study design. Beta diversity will be assessed using permutational multivariate analysis of variance, and differentially abundant taxa will be identified using FDR-controlled methods. Associations between microbial features and clinical measures will be explored using multivariable regression and ordination-based approaches, as appropriate.

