#### Exploratory mechanistic outcomes

3.7.3

Exploratory mechanistic assessments will be conducted according to predefined sampling frameworks. Plasma metabolomic analyses and stool metagenomic analyses will be attempted in all randomized participants who provide usable biological samples at the specified time points (baseline and week 8). Resting-state fMRI and MRS will be conducted in a predefined imaging substudy composed of participants who provide additional consent and have no MRI contraindications. Participation in the imaging substudy is optional and is not required for enrollment in the main randomized trial. We expect that approximately 60 participants of the full cohort will participate in the imaging substudy, depending on consent, eligibility, and scanner availability. These exploratory mechanistic assessments are not formally powered for confirmatory hypothesis testing and are intended to estimate effect sizes, characterize biological patterns, and generate hypotheses for future studies.

The rationale for each exploratory domain is described below. First, disturbances in tryptophan metabolism, particularly within the kynurenine pathway, have been implicated in immune activation, neuroactive metabolite imbalance, and fatigue-related symptoms. Alterations in the KYN/Trp ratio may reflect inflammatory signaling and indoleamine 2,3-dioxygenase activity (Muneer, 2020). Recent CFS studies have suggested abnormal tryptophan catabolism and increased kynurenine production, indicating that tryptophan metabolites may link peripheral dysregulation with central symptoms such as cognitive dysfunction and sleep disturbance (Groven et al., 2021; Hsu et al., 2025). Accordingly, plasma and stool samples will be collected to quantify tryptophan and its downstream metabolites using targeted liquid chromatography-mass spectrometry (LC–MS) (Desmons et al., 2022). Samples will be processed according to standardized laboratory procedures, as described in the online Supplementary materials.

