Beyond evaluating clinical effectiveness, the present study is intended to explore a biologically informed mechanistic framework for CFS. To our knowledge, this integrative design distinguishes the present protocol from most previous CFS trials, which have generally focused on clinical outcomes alone. This trial is also designed as an exploratory mechanistic study focusing primarily on the tryptophan-kynurenine pathway as a candidate link between gastrointestinal disturbance and central symptom expression in CFS. Increasing evidence implicates neuroendocrine–immune dysregulation and the gut-brain axis in CFS, but the relevant causal pathways remain poorly defined. Previous studies have reported altered tryptophan metabolites in cerebrospinal fluid and peripheral samples from patients with CFS, while clinical and microbiome studies have consistently noted gastrointestinal complaints and gut dysbiosis (Walitt et al., 2024; Leong et al., 2022; Gao et al., 2020). Because tryptophan and its downstream catabolites lie at the interface between gut microbial activity, immune signaling, and central nervous system function, the tryptophan–kynurenine pathway represents a biologically plausible focal mechanism linking peripheral disturbance with fatigue-related symptoms. We therefore selected plasma and stool tryptophan-pathway metabolites as the primary exploratory mechanistic domain.

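### Pathway enrichment on a tryptophan-only targeted panel cannot show that the tryptophan pathway stands out; replace it with between-arm estimates from the same samples

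*Protocol article*

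**What the plan says.** Section 3.7.3 (Exploratory mechanistic outcomes) defines the assay: "plasma and stool samples will be collected to quantify tryptophan and its downstream metabolites using targeted liquid chromatography-mass spectrometry". The abstract, the exploratory objective (2.3) and the Discussion describe the outcome in the same terms, and the article names no other metabolite class.

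Section 3.10 (Metabolomics and microbiota analyses) sets out the analysis: "Targeted metabolomics data will be analyzed using multivariate and univariate approaches to identify differential metabolites, with particular focus on the tryptophan pathway". The multivariate part includes principal components and supervised discrimination. The univariate comparisons are FDR-corrected. Then: "Pathway enrichment analyses will then be performed". The article gives no enrichment method and no reference set.

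On status, section 3.10 says "These findings will not be interpreted as confirmatory efficacy evidence". On weight, the Discussion says "We therefore selected plasma and stool tryptophan-pathway metabolites as the primary exploratory mechanistic domain".

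**The concern.** Over-representation analysis asks whether the selected metabolites fall in a pathway more often than the set they could have come from would predict. That question has content only if the measured set contains metabolites both inside and outside the pathway. If every analyte was chosen because it belongs to tryptophan metabolism, every hit lies there by design, and the test result is settled by the assay and the reference set.

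What is at stake is mechanistic interpretation. This is the leading exploratory domain, and the closing part of the Discussion says that clinical improvement together with converging biomarker changes would give preliminary support for larger confirmatory trials. An enrichment result naming tryptophan could be counted as one of those converging signals although it carries no evidence about which pathway responded. Barring confirmatory efficacy claims does not address this, because the misreading would concern mechanism.

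**Working it through.** **The plan's own figures.** The article states no number for the enrichment step, so there is none to reproduce. Its sample size (66 per group, 83 after 20% dropout, 166 in total) reproduces from the stated difference of 1.60 and SD of 3.28, and plays no part here.

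**Inputs.** From the article: the panel is tryptophan-pathway analytes (3.7.3); differential metabolites are selected first and enrichment follows (3.10). Assumed, because the article gives no values: library size, number of pathway members in the library, panel size, and a 5% FDR level.

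**Formula.** With N metabolites in the reference set, K of them in the pathway, and h hits that all lie in the pathway, the hypergeometric p-value is

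p = [K(K−1)…(K−h+1)] / [N(N−1)…(N−h+1)].

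**Reference set = measured panel, all analytes in the pathway.** Then K = N, numerator and denominator are equal, and p = 1 for every h. This needs no assumption about sizes.

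**Reference set = generic library, K = 40.**

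| Hits | N = 500 | N = 2,000 |
|---|---|---|
| 1 | 40/500 = 0.08 | 40/2,000 = 0.02 |
| 2 | (40×39)/(500×499) = 0.0063 | (40×39)/(2,000×1,999) = 0.00039 |
| 3 | (40×39×38)/(500×499×498) = 0.00048 | (40×39×38)/(2,000×1,999×1,998) = 0.0000074 |

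One hit is enough for p < 0.05 in the larger library but not in the smaller one. Two hits are enough in both. A less favourable case, K = 80 in N = 1,500, gives 80/1,500 = 0.053 for one hit and (80×79)/(1,500×1,499) = 0.0028 for two. The formula does not ask whether the hits are true or false.

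**How often hits arise with no treatment effect.** Simulation of the global null: 20,000 runs for each of 10, 20 and 30 analytes, at correlation 0 and 0.5.

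| Selection rule | At least 1 hit | At least 2 hits |
|---|---|---|
| Benjamini-Hochberg at 5% | about 4–5% | about 0.4–2% |
| Uncorrected p < 0.05 | about 29–79% | about 9–45% |

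The first row matches the rule that section 3.10 gives for univariate comparisons. The second would matter only if uncorrected p-values decided which metabolites go forward. Section 3.10 states no error control for the supervised discrimination route.

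**If the panel is wider.** Suppose 20 tryptophan analytes among 60 or 200 measured, with the measured set as reference. Two hits, both in the pathway, give (20×19)/(60×59) = 0.11 and (20×19)/(200×199) = 0.0095. The p-value now depends on where the hits fall, so the test is no longer degenerate.

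**The case against.** A reader might infer that the analysis will report tryptophan enrichment whatever Tuina does. The document does not support that. Selection by FDR-corrected univariate tests comes before enrichment, and with no effect it leaves at least one metabolite in only about 4–5% of trials at an assumed 5% level. A significant result also requires a generic library as reference; against the measured panel it can never occur. A false-positive rate based on uncorrected p-values would describe a rule that section 3.10 does not set for its univariate comparisons.

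Three further objections deserve weight.

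- *Method not named.* The article does not say over-representation analysis. A self-contained test, which asks whether a set of metabolites differs between arms, needs no reference set and is not degenerate here; nor is a comparison among sub-branches. This stands: the point applies to enrichment tests that compare a pathway with a background, and the alternatives belong in the remedy.
- *Panel may be wider.* The clause in section 3.10 about focusing on the tryptophan pathway can be read as allowing other analytes, and the supplement is not shown. It is a possible reading, but section 3.7.3 describes the assay without naming any other class.
- *Exploratory status.* The article is careful to disclaim confirmatory and causal claims. That limits the consequence, but it does not give the test information that it lacks.

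A reader might also infer that KYN/Trp has been dropped, because section 3.10 does not name it. The article mentions the ratio as rationale ("Alterations in the KYN/Trp ratio may reflect inflammatory signaling and indoleamine 2,3-dioxygenase activity"), and a condensed article need not list every derived parameter. That is no error in the plan.

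**Conclusion.** The point holds: section 3.10 states an analysis that does not fit the assay stated in section 3.7.3. If the panel is confined to tryptophan metabolism and enrichment means over-representation, the result is either p = 1 in every case or tilted toward tryptophan by the choice of library, with p of about 0.006 to 0.0004 for two hits under the assumed sizes. The p = 1 result rests only on the panel's composition; the library figures rest on assumed library and pathway sizes. When there is no effect, FDR selection makes a spurious enrichment uncommon. When there is an effect, the evidence lies in the individual metabolite comparisons, and enrichment adds nothing about which pathway is involved.

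The impact stays within the exploratory mechanistic analysis. The FS-14 comparison, the sample size and the clinical conclusions are untouched. Because this is the leading mechanistic domain and the correction is nearly free, it should be made.

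**What to change.** In section 3.10, remove over-representation analysis for the tryptophan-targeted panel and put one of these in its place:

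1. Between-arm differences at week 8, with confidence intervals, in a short prespecified list of substrate-product ratios: for example plasma KYN/Trp, followed by a few ratios for the kynurenine, serotonin and indole branches. This serves the section's own aim of estimating effect sizes.
2. A self-contained global test between groups for each sub-branch.

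If the panel does extend beyond tryptophan metabolism, say so in section 3.7.3 and keep enrichment only with the measured analytes as the reference set.

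Cost: a wording change, with no new samples or assays. What is lost is an enrichment plot that would carry no information about pathway choice.
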